## Discussion

To our knowledge, this is the first trial aiming to solve the problem of limited overall effect and migration effect of working memory training in schizophrenia by performing professional training, which is based on changing the neuroplasticity of working memory-related brain areas through iTBS primitively.

This trial has several advantages. First, this study use iTBS stimulation, which is currently a well-evidentiary and efficient way to alter the plasticity of the brain, as a tool to regulate the functional state of brain regions before working memory training. The effects of iTBS on brain function and structural plasticity in schizophrenia were investigated by structural and functional MRI.

Second, we hypothesize that iBTS stimulation, which will be able to alter brain plasticity, will facilitate (enhance) the clinical effects of working memory training on improving cognitive function of schizophrenia? This is a key issue in the study of WMT mechanism, that is, whether the way of “preheating (iTBS stimulation activates local neuronal activity first) and then ironning (working memory training)” can make “iron better tempered” (the changes of brain function and structure are more significant). In our study, the WMT control group (iTBS+SRT) and iTBS control group (sham iTBS+WMT), were set up to compare with the study group, respectively, and to analyze the differences of brain plasticity, to explore whether the training of “preheating and then ironning” (iTBS+WMT) is superior to that of “ironning without preheating” (sham iTBS+WMT) and “ironning without preheating” (iTBS+SRT) in changing the neuroplasticity (function and structure) and to provide a scientific basis for exploring ways to enhance the neuroplasticity of the brain and improve its function.

Another advantage of this trial is to explore the migration effect, that is, whether training can improve untrained cognitive ability as well as related-cognitive processing ability, such as whether it can improve logical reasoning ability after working memory training? The training for the normal youngs suggests that working memory training alone can improve memory function and fluid intelligence, thus verifying the existence of migration effect of working memory training. However, there are few studies on whether the migration effect occurs in schizophrenia, and this study makes up for the shortcomings in this area.

This sample cannot entirely represent a population combining comorbidities with considerable treatment heterogeneity. However, we opted to the rigorous inclusion, exclusion, and dropping criteria in order to acquire fewer confusing variables and make trial more accuracy and truthfulness.

## Trial status

Patient recruitment is currently ongoing. This is the first version of this protocol (V1.0). If the protocol needs to be amended, we should notify firstly the sponsor and the centers. After passing the ethics committee review, a copy of the revised protocol will be sent to the managers of two centers and be added to the web for record accurately. The first patient has been enrolled on December 23, 2019, and it is expected to finish by the end of 2020. Due to the impact of COVID-19, our related researches have been severely affected, and the end time will be appropriately postponed.

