### Dropping criteria

Total ten sessions not to finish the training among four groupsThe relapse or aggravation of the disease needing the replacement of antipsychotic drugs

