**Fig. 1 Fig1:**

The iTBS+WMT group

iTBS (provided by YiRuiDe CCY-II therapeutic instrument, Wuhan, China) used standard international-approved parameters (120% RMT stimulation intensity or 40% intensity; triplet 50 Hz bursts, repeated at 5 Hz; 2 s on and 8 s off; repeat 20 times; 600 pulses per session; total duration of 3 min 20 s) [25, 29, 30]. After professional testing, the magnetic field intensity has reached the effective range. The left dorsolateral prefrontal cortex is located in each patient with a positioning hat, which was previously proved as optimal target on the basis of clinical finding and whole brain MRI [31]. Initial treatment comprised 30 sessions in total, which consisted of once-daily sessions (on weekdays; i.e., five sessions a week).

The WMT training tool belongs to a computer training system based on the working memory theory model and cognitive processing process that is self-developed and validated by pre-clinical studies. This set of training shows the most typical working memory paradigm, that is, the subjects try to memorize a series of continuous materials (including numbers, languages, pictures) of random length (length is not fixed), and judge the sequence of the last 2–4 materials after presentation. The total number of working memory training sessions is 30, 40 min each, five times a week for 6 weeks.

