### Sample size

The hypothesis is 77.2% response rate in the cognitive training group and 41.4% in the control group on our preliminary studies [32]. The difference between the two groups was improved about 35.8%, as the basis for calculation. With a statistical power of 80% and a significance level of 5%, the minimum sample size of 28 subjects is required in each group. With our previous research experience, we allow for a maximum dropout rate of 20%. The study adopts the block randomization to divide into groups with 8 patients in each block. The actual minimum sample size of each group was 34 cases. Combining each center clinical states, Beijing center inclusion number has been set to 120 patients to participate into this research and Shenyang center has 80 patients.

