### Statistical analysis

The analysis will be conducted on the basis of the intent-to-treat (ITT) principle. Some descriptive analysis of the data gathered during each assessment will be carried out precisely until the final assessment. Special time points for analysis are the baseline, end of iTBS or sham iTBS sessions, and 3 and 6 months after the final treatment. Median and range describe continuous variables, and frequencies and percentages describe qualitative variables.

We will accept a significance level of 5% (*P* < 0.05) corrected for multiple comparisons when needed. To assess our primary endpoint criterion, i.e., cognitive performance changes on the task, outcomes at four time points will be compared using repeated measurement analysis of variance of variance with time (baseline, ending, and 3 and 6 months after the final treatment) and group (study group (iTBS+WMT), WMS control group (iTBS+SRT), iTBS control group (sham iTBS+WMT), and placebo control (sham iTBS+SRT)) as factors. Further comparison between the two groups can show the simple iTBS effect, the simple WMT effect, and the facilitation effect of iTBS on WMT. Sensitivity analyses will explore the impact of imputation of data losses including loss to follow-up and dropout.

In the case that the data do not meet the normal distribution assumption, the non-parametric Mann-Whitney test will be used to compare performance improvements between four groups. SPM will be used to analyze imaging data to detect any changes in brain function and structure caused by cognitive training.

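### The dropping criteria act after randomisation and are presented as cleaning the sample, which conflicts with the stated ITT analysis; the ten-session rule can also be read two ways

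*Protocol article*

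**What the plan says.** All references are to the protocol article.

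- **Dropping criteria.** There are two. The first ties dropping to ten sessions and to not finishing the training, in all four groups. The second is "relapse or aggravation of the disease needing the replacement of antipsychotic drugs". Neither says what happens to a dropped patient's later assessments or data.
- **Intervention (text under Fig. 1).** For stimulation: "Initial treatment comprised 30 sessions in total, which consisted of once-daily sessions (on weekdays; i.e., five sessions a week". For training: "The total number of working memory training sessions is 30, 40 min each, five times a week for 6 weeks".
- **Statistical analysis.** "The analysis will be conducted on the basis of the intent-to-treat (ITT) principle". The primary comparison is a repeated-measures ANOVA with group and four time points. Dropout appears once more: "Sensitivity analyses will explore the impact of imputation of data losses including loss to follow-up and dropout".
- **Discussion, closing paragraph.** The inclusion, exclusion and dropping criteria are named together as a deliberate choice to limit confounding and make the trial more accurate.
- **Sample size.** 28 per group before dropout and 34 after; on dropout, "we allow for a maximum dropout rate of 20" per cent.
- **Trial status.** "Due to the impact of COVID-19, our related researches have been severely affected, and the end time will be appropriately postponed".

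**The concern.** Entry criteria act before allocation and cannot bias the comparison between arms. Dropping criteria act after it, and both of these depend on what happens during treatment. Missed sessions can reflect tolerability: the Data monitoring section expects mild effects such as headache and irritability and lets patients opt out. Relapse reflects clinical course. Either may differ between real and sham stimulation, which is the contrast that tests whether iTBS facilitates working memory training. An ITT analysis exists to prevent selection on such events, yet the Discussion presents the dropping criteria as a way of obtaining a cleaner sample.

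The ambiguous session rule adds a second problem. Two centres apply it, and they could apply different rules while both believing that they follow the protocol.

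**Working it through.** **1. The plan's own figures.** Inputs from Sample size: response 77.2% versus 41.4%, power 80%, significance level 5% (two-sided assumed, as sidedness is not stated). The pooled normal formula without continuity correction gives 29 per group and the arcsine formula 28.05, so the stated 28 is reproduced. For dropout, 28 × 1.2 = 33.6, rounded up to the stated 34; 28 / 0.8 = 35. The difference is immaterial here.

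**2. The session rule.** The course is 5 per week × 6 weeks = 30 sessions.

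- Reading A, ten sessions missed: met at 10 missed, and 10 / 30 = 33% of the course.
- Reading B, fewer than ten sessions completed: at most 9 completed, so at least 30 − 9 = 21 missed, and 21 / 5 = 4.2 weeks.

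A patient who completes between 10 and 20 sessions is dropped under A and kept under B.

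**3. The sections side by side.**

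- Dropping criteria: patients are dropped on post-randomisation events.
- Discussion: these criteria shape the sample, alongside the entry criteria.
- Randomization: a participant whose blind is broken is treated as outside the trial, so removal after allocation is contemplated elsewhere too.
- Follow-up and Data collection: assessments are set at post-treatment, 3 and 6 months; neither section says whether a dropped patient still attends.
- Statistical analysis: ITT is stated; imputation for dropout is confined to sensitivity analyses. A classical repeated-measures ANOVA uses only patients with all four measurements, so a patient dropped during the course and not assessed again would fall out of the primary analysis in that form.

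**4. Size of the possible bias.** If dropped patients are left out, and do δ worse than the others in either arm, the mean of those who remain exceeds the arm's full mean by p × δ, where p is the proportion dropped. The bias in a contrast is therefore (p1 − p2) × δ. All inputs here are assumed: 20% to 30% dropped in one arm, 10% in the other, and δ of 0.3 to 0.8 SD.

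- Low end: (0.20 − 0.10) × 0.3 = 0.03 SD.
- High end: (0.30 − 0.10) × 0.8 = 0.16 SD.

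**5. Does loss of numbers matter?** 200 patients allocated 1:1:1:1 give 50 per group. The required 28 remain until dropout reaches 1 − 28 / 50 = 44%. Power for the plan's own response rates, two-sided, is 96.5% with 50 per group, 91.8% with 40 (20% dropout), 82.3% with 30 (40%) and 79.5% with 28 (44%). On the plan's own calculation, the issue is selection rather than sample size.

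**The case against.** The strongest reply is that the conflict is not proven. Dropping may mean only that treatment stops. Imputing for dropout suggests that dropouts remain in the analysis set, the Follow-up section does not limit assessments to completers, and reminder calls and subsidies are planned to keep patients attending. A condensed article may also leave such detail to a fuller document. No section reports differential dropping, and the bias range is entirely assumed.

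Much of this stands. The milder reading is possible, and the size of the bias is unknown. But the dropping criteria are a stated rule rather than an omitted detail, the Discussion states their purpose as shaping the sample, and the imputation sentence does not reach the primary analysis.

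A stronger reading is tempting. A reader might infer from Trial status that pandemic closures trigger the session rule, since 2 weeks × 5 sessions = 10, and so use up the 20% allowance. The document does not support this:

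- Trial status reports disruption and a later end date. That fits paused recruitment equally well; no interrupted course or dropped patient is mentioned.
- The arithmetic needs reading A and no make-up sessions, on which the document is silent.
- Finishing by 31 December 2020, less 183 days of follow-up and 42 of treatment, puts the last enrolment at 20 May 2020, 149 days after the first. Steady accrual then gives 200 × 42 / 149 = 56 patients (28%) in treatment at once. That timetable has been given up. Over an assumed 12 to 24 months the figure is about 23 to 12 patients (12% to 6%).
- Blocks of eight by enrolment time within centre would largely balance closures across arms.
- The 20% is a planning allowance, and the enrolled numbers tolerate more.

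**Conclusion.** The point holds in a limited form. Followed as written and as the Discussion explains them, the dropping criteria select patients on post-randomisation adherence and relapse, which conflicts with the ITT statement. The conflict takes effect if dropped patients leave the assessments or the primary ANOVA, which the article neither states nor rules out. The bias cannot be derived from the document; 0.03 to 0.16 SD illustrates the assumed inputs and is no estimate for this trial. The ambiguity of the session rule, 10 missed against 21 or more missed out of 30, needs no assumption beyond the stated schedule. No claim is made that closures have dropped patients, that the 20% allowance is exhausted, or that power is lost.

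**What to change.** Reconcile the Dropping criteria, Statistical analysis and Discussion sections:

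1. State that meeting a dropping criterion ends neither the post-treatment, 3-month and 6-month assessments nor inclusion in the primary analysis as randomised.
2. Settle which reading of the ten-session rule is meant, and word it so that both centres apply it alike.
3. Record in the eCRF the number of sessions completed and the reason for each missed one.
4. Use the dropping criteria only to define a labelled per-protocol sensitivity analysis, and amend the Discussion sentence to match.

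Whether and when treatment itself stops is left to the investigators. The cost is protocol wording, a small eCRF addition and one sensitivity analysis. The downside is some effort to bring back patients who have stopped their sessions. Recruitment was ongoing when the article was written, so the change is best made before more patients meet a criterion.

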## Data Availability

The datasets are available from the corresponding author on reasonable request.

## Abbreviations

rTMS: Repetitive transcranial magnetic stimulation
iTBS: Intermittent theta burst stimulation
CONSORT: Consolidated Standards of Reporting Trials
MRI: Magnetic resonance imaging
LTP: Long-term potentiation
LTD: Long-term depression
WMT: Working memory training
SRT: Simple Response Training
MCCB: MATRICS Consensus Cognitive Battery
PANSS: Positive And Negative Syndrome Scale
WAIS-R: Wechsler Adult Intelligence Test Brief Version
BNSS: Brief Negative Symptom Scale
CGI: Clinical Global Impression
PSP: Personal and Social Performance Scale
TEPS: Temporal Experience of Pleasure Scale
SQOLS: Quality of Life Scale
SES: Self-Esteem Scale; the visual analogue scale (VAS) of side effects
HVLT: Hopkins Verbal Learning and Memory Test
BVMT: Brief Visuospatial Memory Test
VERT: Verbal Emotion Recognition Test
CPT: Continuous Performance Test
SPIRIT: Standard Protocol Items: Recommendations For Interventional Trials
eCRF: Electronic case report form
ID: Intellectual disability
